#### Eligibility criteria and recruitment

For H-HOPE and Pre-H-HOPE Consented parent-infant dyads, infants are eligible if they are born at 23–35 weeks gestational age, at least 31–32 weeks PMA, and clinically stable. Parents are mothers, fathers, or other significant family member who intend to act in the role of a parent, regardless of biological relationship to the infant, gender identity or sexual orientation. In most cases the biological mother is identified as the primary parent and she will be asked to name the second parent. The Non-Consented Pre-H-HOPE Infants must meet the same infant criteria, however no parents are involved.

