#### Sample size and power for aim 2 effectiveness

Based on participating sites’ data, 542 infants will be eligible for the H-HOPE cohort during the 6-month Executing phase. Of the available infants, we expect to enroll at least 70% (*n* = 379 parent-infant pairs) and to retain 265 through 6-weeks following the infant’s discharge. During a 12-month period before H-HOPE implementation, 1084 eligible infants will be available for the Pre-H-HOPE Comparison Cohort in two sub-cohorts.

The first sub-cohort, the Consented Pre-H-HOPE Parent-Infant Units, is recruited at the same time as the Planning and Engaging phase at each site and will contribute to all outcome analyses (*n* = 542). The retention rates will be the same in the Consented Pre-H-HOPE sub-cohort and the H-HOPE cohort (*n* = 265). The second sub-cohort, the Non-Consented Pre-H-HOPE Infants (*n* = 542), will contribute only retrospective infant growth and cost data obtained from de-identified EHR and cost records in the 6 months prior to the start of Planning and Engaging. Based on our prior research, near medium to large effect sizes are expected for the primary outcomes of infant growth and health care utilization following discharge [49, 57] and the secondary hospital cost outcome [58]. Using the STATA package *stepped wedge* [84], the power analysis found that there will be at least 80% of power to detect a medium effect of Cohen’s *d* = − 0.50 at a significance level of α = .05 in this stepped wedge design with 4 sites and an average of at least 50 subjects per site (or 200 in total) across 4 staggered time points, assuming the intra-class correlation coefficient (ICC) is .1, a common ICC found in health and behavioral research [85, 86]. Assuming ICC as .05, which is common ICC health cost analysis [87–89], research would require at least 30 subjects per site (or 120 in total). Thus, in this proposed study, the anticipated total sample size of 265 will be adequate to detect a medium effect for all outcome measures.

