### Measures

#### Aim 1 primary implementation outcome measures

We examine three measures of success recommended for late-phase implementation by Proctor et al. [72]. Sustainability measures whether the site is providing H-HOPE. Reach measures the proportion of eligible parent-infant units who receive H-HOPE at that site. Degree of Implementation measures the mean H-HOPE services received per parent-infant unit. The research team will consult with each site to build within the EHR infant eligibility for H-HOPE, documentation of Massage+ and the parent participatory guidance sessions. These success measures will be obtained from each site’s EHR which will record eligibility and receipt of H-HOPE parent and infant services. If the site chooses to discontinue H-HOPE, we will conduct the final interview and end evaluation.

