The Quantitative Data Center provides oversight and coordination for all quantitative data-related operations and conducts the quantitative data analyses for Aim 1 (degree of implementation) and Aim 2 (effectiveness). Prior to Planning and Engaging, the Center works with each site’s informatics team to modify their EHR build so the H-HOPE eligibility, initiation and specific services received can be documented directly in the EHR. The Center also oversees the REDCap database construction and management for participant screening, study enrollment, eConsenting, study monitoring, and quantitative data collection. During implementation at each site, the Center works closely with each site to obtain relevant data throughout the study, shares site results and helps prepare the report that the site administrative team will use to decide whether to continue H-HOPE as the standard of care. Each site has a H-HOPE research team that is responsible for consenting both pre-H-HOPE and H-HOPE parents, facilitating and monitoring data collection, and coordinating data collection and transfer with the data Centers.

The Qualitative and Mixed Methods Data Center manages and analyzes all qualitative and mixed methods data-related operations. The primary focus of the Center is ongoing mixed methods data analysis and interpretation to address Aim 3. The qualitative interview data are managed within the Center and analyzed as described below. The relevant quantitative data are obtained from the Quantitative Data Center. At each site, the Center works with the H-HOPE team to obtain H-HOPE team meeting records and to complete interviews with selected hospital personnel and selected H-Hope parents.

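### The start of the cost window is recorded prospectively for H-HOPE infants but must be inferred for the retrospective comparison infants, and no common dating rule is stated

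*Protocol article*

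**What the plan says.** All references are to the protocol article.

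- **EHR build.** Under Overall study coordination, before the Planning and Engaging phase each site is to "modify their EHR build so the H-HOPE eligibility, initiation and specific services received can be documented directly in the EHR". No go-live date or lead time is given.
- **Use of the new record.** Under Aim 1 primary implementation outcome measures: "These success measures will be obtained from each site’s EHR which will record eligibility and receipt of H-HOPE parent and infant services". Screening and enrolment of consented participants are handled in REDCap (Overall study coordination).
- **Retrospective comparators.** Under Sample size and power for aim 2 effectiveness, the Non-Consented Pre-H-HOPE infants "will contribute only retrospective infant growth and cost data obtained from de-identified EHR and cost records in the 6 months prior to the start of" the first implementation phase (Planning and Engaging). There are 542 of them.
- **Criteria.** Under Eligibility criteria and recruitment: "The Non-Consented Pre-H-HOPE Infants must meet the same infant criteria". Those criteria are gestational age at birth of 23–35 weeks, post-menstrual age (PMA) of at least 31–32 weeks, and clinical stability, which the article does not define.
- **Outcome windows.** Hypothesis H2b and the text of Aim 2 effectiveness outcome measures start the cost window when the infant enters H-HOPE. Table 2 starts it when the infant becomes eligible. Growth runs from birth to discharge.
- **Matching.** Under Aim 2 analysis, each H-HOPE infant is matched on propensity score to a pre-H-HOPE infant for growth and cost.

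**The concern.** Cost per day averages over a window, so it depends on which days the window contains. If early days cost more or less than later ones, moving the start by a few days changes the result without any change in care.

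For H-HOPE infants the day of eligibility or initiation is recorded as it happens. A retrospective infant has no day of entry and, unless the build went live up to six months early, no contemporaneous eligibility entry. Gestational age and PMA can be read from any chart, but stability and its date have to be reconstructed. Matching balances infant and parent characteristics. It does not align a start day that was set in two different ways.

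At stake is the comparison behind the cost-saving claim. The Markov model also draws on the hospitalization cost estimates (Aim 2 analysis), so an error in the start date could carry into the 5-year projection.

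**Working it through.** **1. The plan's own figure.** 542 (consented sub-cohort) + 542 (retrospective sub-cohort) = 1084, as stated.

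**2. Share of the pool without a contemporaneous eligibility record.**
- As stated: 542 / 1084 = 50%.
- Assuming 70% of the consented sub-cohort enrols, as in the H-HOPE cohort (379): 542 / (542 + 379) = 542 / 921 = 59%.
- Assuming only the 265 retained count: 542 / (542 + 265) = 542 / 807 = 67%.

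**3. Which anchor exists for whom.**

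| Cohort | Day of entry into H-HOPE | Eligibility day recorded prospectively |
|---|---|---|
| H-HOPE | yes | yes |
| Consented Pre-H-HOPE (recruited during Planning and Engaging, after the build) | none | possible, by EHR field or screening |
| Non-Consented Pre-H-HOPE (6 months before) | none | no, or only a late part if the build went live early |

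The entry anchor exists for no comparison infant. The eligibility anchor can exist for all, but not from the same kind of record.

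**4. Where stability alone sets the date.** An infant born at 33–35 weeks already meets the PMA criterion at birth. For such an infant stability is the only criterion that can move the start. If it cannot be recovered from the record and PMA is used alone, the start becomes the day of birth.

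**5. Sensitivity of cost per day (all inputs assumed; the documents give none).** Take 28 days from true eligibility to discharge.

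*Start dated L days too early*, with those days costing r times the later ones: relative change = (28 + L·r) / (28 + L) − 1.
- L = 3, r = 1.25: 31.75 / 31 − 1 = +2.4%
- L = 7, r = 1.5: 38.5 / 35 − 1 = +10.0%
- L = 10, r = 2: 48 / 38 − 1 = +26.3%

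*Start dated L days too late*, with the omitted days costing r times the rest: relative change = 28 / (28 + L·(r − 1)) − 1.
- L = 3, r = 1.25: 28 / 28.75 − 1 = −2.6%
- L = 7, r = 1.5: 28 / 31.5 − 1 = −11.1%
- L = 10, r = 2: 28 / 38 − 1 = −26.3%

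These are changes for one affected infant. If half the matched comparators are retrospective and all of those are misdated, the comparator average moves by about half as much: +1.2%, +5.0% and +13.2% for early dating; −1.3%, −5.6% and −13.2% for late dating.

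**The case against.** The strongest reply is that the article nowhere says the retrospective infants are classified or dated by a different method. It requires the same infant criteria. It ties the new EHR field to the Aim 1 measures, not to Aim 2, and places screening in REDCap. Stability is undefined, so the build itself may rest on routinely charted items. An extraction rule is also the kind of detail a condensed article leaves to the full protocol or analysis plan.

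Much of this stands. A reader might infer that two methods are fixed in the plan, but the documents show only that no common method is stated and that the new field cannot supply one for the earlier months. A reader might also infer that the primary growth result is misdated. It is not, because its window opens at birth. The matching pool also contains consented infants recruited after the build, so only part of the comparison is affected.

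The reply does not remove the cost problem. Whether H-HOPE infants are dated through the EHR field or through REDCap, the record is prospective, and the retrospective infants have neither. The two start definitions are printed in the article itself, and one of them cannot be applied to any comparison infant. That is a badly fixed outcome definition, not just omitted detail.

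**Conclusion.** The point holds for the secondary cost outcome. Following the stated anchors can give matched groups systematically different start days, and matching cannot repair this. The comparators concerned are 50% of the pool as stated, and 59% to 67% under the enrolment and retention assumptions above.

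The effect on cost per day cannot be computed from the documents. The percentages in the working only illustrate its scale under assumed inputs, and the larger ones apply to a single affected infant, not to the comparator mean. It is tempting to conclude that the design favours H-HOPE by construction, because falling back on PMA would bring early, intensive days into the comparison cohort. That is one possibility. A cautious charted proxy for stability could date eligibility late and push the bias the other way, and the documents establish neither.

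For growth, the only exposure is through which infants are classed as eligible. Matching may partly address that, since gestational age, the Neurobiological Risk Score and days of ventilation are among the infant characteristics the article lists.

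The conclusion assumes that the build did not go live a full six months before Planning and Engaging. The article does not say that it did.

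**What to change.** 1. Reconcile entry with eligibility as the start of the cost window in H2b, the outcome text and Table 2. The chosen anchor must be definable for infants who never receive H-HOPE.
2. For the matched growth and cost analyses, derive eligibility and the cost start date for every infant in all cohorts, H-HOPE included, by one prespecified algorithm. It should use only EHR items routinely charted in all periods. List those items before the de-identified extract is requested, since later chart review may not be possible.
3. In the consented cohorts, report agreement between the algorithm and the prospective record, for both eligibility status and date.
4. Add a sensitivity analysis of growth and cost without the retrospective sub-cohort.

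The cost is analysis-plan wording and one extraction specification. Recruitment and care do not change, and Study status says that no site has started and no subjects have been enrolled. The downside is that an algorithm-derived date is coarser than a prospective flag, and the sensitivity analysis has a smaller matching pool.

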### Analysis plan

#### Aim 1 analysis

Aim 1 measures, Sustainability, Reach, and Degree of Implementation, are analyzed by the Quantitative Data Center, using descriptive statistics and visual displays.

#### Aim 2 analysis

Aim 2 evaluates the effectiveness of H-HOPE including infant growth, health care utilization following discharge, infant hospital costs. Aim 2 also explores the impact of H-HOPE on parent outcomes detailed in Table 2*(exploratory outcomes)*. The Quantitative Data Center analyzes Aim 2 measures.

Before analytic modeling, propensity score methods [101–104] will be utilized to reduce any selection bias by ensuring balanced distributions of infant and primary parent characteristics between Pre-H-HOPE and H-HOPE infants. For the growth and infant hospital costs outcomes, propensity scores will first be computed using available infant and parent characteristics. Then, pairs of infants will be created by matching each infant in the H-HOPE cohort with an infant in the pre-H-HOPE cohort with the same or most similar propensity scores. The final analytical models will be applied directly to propensity-score-matched pairs.

For the other Aim 2 outcomes, including health care utilization from discharge through 6-weeks post discharge and the exploratory parent outcomes, data are collected directly from parents and are not available in hospital records. Therefore, propensity score weighting will be used. In propensity score weighting, propensity scores will first be computed similarly to propensity score matching. Then propensity scores will be used to calculate inverse probability of treatment weights as weighting scores, rather than matching samples (i.e., infants or parents). The propensity weighting scores will be incorporated in weighted final analytical models preserving the entire sample for final analytical modeling.

In all the final analytical modeling, linear mixed models will be utilized to analyze normally distributed outcomes [80, 105] (e.g., infant growth and parent outcomes). Linear mixed models are an extension of linear regression models to allow estimating both between-site and within-site effects when there is a nested data structure (e.g., individual patients/infants are nested within sites). Generalized linear mixed models, an extension of linear mixed models, will be used to analyze non-normally distributed outcome measures (e.g., infant health care utilization, hospital costs).

In order for new hospitals or health systems to make informed decisions about implementation, we will estimate the incremental costs of implementing H-HOPE using a Markov state-transition model over a 5-year time horizon from the perspective of an individual hospital or health system, using standard methods [57, 106, 107]. Total implementation costs will be derived from (1) H-HOPE initial implementation costs using the observed number of hours spent for training multiplied by national estimates of hourly NICU nursing salary, (2) H-HOPE infant intervention delivery costs estimated from the propensity-weighted hospitalization costs, and (3) costs of infant healthcare utilization (number of visits multiplied by the average cost of each type of visit). In subsequent years, the costs of ongoing training will be reduced based on estimates of the number of new staff needing training. Both probabilistic and deterministic analyses will address the effect of uncertainty in cost and effectiveness estimates on the decision to implement H-HOPE, including (a) identifying the plausible values for effectiveness where H-HOPE does not result in net cost-savings over a 5 year time horizon, and (b) if cost-savings are reached within 5 years, the time for achieving cost-neutrality. Additional sensitivity analyses will examine the effects of varying assumptions about NICU admission volume and staff turnover.

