**Fig. 1 Fig1:**
[figure not shown]
Incomplete Stepped Wedge Design. Pre-I & P = 6 months of pre-implementation plus Planning and Engaging during which Pre-H-HOPE Comparison Cohort Data are collected simultaneously, E = 6 months of Executing at the end of which posttest will be taken, R = 2 months of Reflecting and Evaluating, S = 6 months of Sustaining. The order of implementation was randomly assigned

To evaluate effectiveness, we chose not to use a randomized design with simultaneous intervention and control comparison groups because it would be confusing for nursery staff and parents to have two different standards of care. Because this is an implementation study, H-HOPE will be introduced as the standard of care. All eligible infants will receive H-HOPE whether or not their parents enroll in the research study. Instead, we compare parent and infant outcomes before and after the introduction of H-HOPE at each site.

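### For growth and cost, the propensity score aims to balance parent characteristics that about half of the comparator pool does not have, and consent selection is partly one-sided

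*Protocol article*

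**What the plan says.** **Comparators.** Under Sample, the Pre-H-HOPE cohort has two parts: consented parent-infant units with full data, and non-consented infants with de-identified existing growth and cost data. The second part was added so that matching would have enough infants. Eligibility criteria and recruitment states: "The Non-Consented Pre-H-HOPE Infants must meet the same infant criteria, however no parents are involved". The sample-size section puts it at 542 infants from the six months before Planning and Engaging.

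**Treated side.** "542 infants will be eligible for the H-HOPE cohort during the 6-month Executing phase", of whom 70% (379 pairs) are expected to enrol. The text below Fig. 1 adds: "All eligible infants will receive H-HOPE whether or not their parents enroll in the research study".

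**Method.** The Aim 2 analysis sets out to balance infant and primary parent characteristics between cohorts. For growth and cost, "propensity scores will first be computed using available infant and parent characteristics", and pairs are then formed by "matching each infant in the H-HOPE cohort with an infant in the pre-H-HOPE cohort". The other outcomes are weighted. The cost-model paragraph nevertheless lists "H-HOPE infant intervention delivery costs estimated from the propensity-weighted hospitalization costs" as an input.

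**The concern.** A propensity score needs the same variables on both sides. The infants brought in to make matching workable are the ones without parent data, so the plan can be followed in only two ways. If parent variables enter the score, those infants cannot be scored and drop out. If parent variables are left out, the infants stay but the stated balance on parents is not achieved.

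The second route matters because the missing variables (education, income and similar) are plausible correlates of consent. Treated infants come only from consenting families, while the retrospective comparators come from consenting and non-consenting families alike. Any difference in growth or cost linked to consent and not explained by infant covariates then becomes part of the estimated H-HOPE effect. The results also feed each site's report on continuing the programme (Overall study coordination) and the five-year cost model.

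**Working it through.** **1. Counts.** 542 × 0.70 = 379.4, the stated 379. 2 × 542 = 1084, the stated 12-month pool. Both reproduce.

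**2. Share of the pool without parent data.** The sample-size section prints n = 542 for the consented sub-cohort, which is every eligible infant. At the 70% enrolment assumed for H-HOPE it would be 379.
- Printed count: 542 / 1084 = 50%.
- 70% enrolment: 542 / (379 + 542) = 542 / 921 = 59%.

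**3. Bias from one-sided selection.** Let consenters and refusers differ by δ SD after infant covariates. The documents give no δ, so 0.1 to 0.5 SD is an assumption. All eligible infants then differ from consenters by 0.3δ. If matched comparators are drawn in proportion to the pool, bias = 0.3 × δ × share.

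| δ (SD) | Bias, share 50% | Bias, share 59% |
|---|---|---|
| 0.1 | 0.015 | 0.018 |
| 0.2 | 0.030 | 0.035 |
| 0.3 | 0.045 | 0.053 |
| 0.5 | 0.075 | 0.088 |

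**4. Bias against the standard error (59% share).**
- Ignoring clustering, 379 pairs give SE = √(2/379) = 0.073 SD. For δ = 0.1, 0.2, 0.3 and 0.5 the two-sided 5% test then has true type I error of about 5.7%, 7.7%, 11% and 23%.
- With period effects, ICC 0.1, 12 months before and 6 months after the start at each of four sites, Table 1 site sizes and an assumed stagger of 2 to 6 months, the SE is 0.144 to 0.172. At a 3-month stagger it is 0.153, so δ = 0.3 gives 0.053 / 0.153 = 0.35 SE, against 0.053 / 0.073 = 0.7 SE unclustered. Type I error at δ = 0.5 is then about 9%.

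**5. Precision of 1:1 matching.** Pairing 379 infants leaves 921 − 379 = 542 comparators unused (59%). Keeping all 921 gives SE = √(1/379 + 1/921) = 0.061 against 0.073, which is 16% smaller before clustering and variance inflation from unequal weights. The 379 pairs already detect 2.80 × 0.073 = 0.20 SD with 80% power on the same unclustered basis, well below the planned 0.50.

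**The case against.** The best defence is the word *available*: it permits a score built on whatever all sub-cohorts share, and the exact variable list is detail that an article leaves to the full protocol or SAP. That is fair as far as the list goes. It does not remove the conflict, because the same section sets balance on the primary parent as the purpose of the score, and no choice of list achieves that for infants without parent data.

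Four stronger readings are tempting, and the documents do not support them.
- *The whole comparator is unselected and lacks parent data.* It also contains consented units recruited during Planning and Engaging with full parent data, so the problem touches 50% to 59% of the pool.
- *Matching is pooled across NICUs.* The article is silent on this, and the final models nest infants within sites.
- *1:1 matching wrongly wastes data.* Unused controls are normal in a matching reservoir, and the loss is immaterial at the planned effect size.
- *The records already allow all eligible infants on both sides.* Every eligible infant receives H-HOPE, but the only H-HOPE-era data described without individual consent are the aggregated Aim 1 data, and costs come from separate hospital cost records. Individual data on families who declined are not documented as available.

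**Conclusion.** The stated balance goal and the stated comparator data cannot both hold for growth and cost. Following the text either loses the infants that the match was built on or leaves consent-related differences unbalanced in a primary outcome. On an assumed consenter-refuser difference of 0.1 to 0.5 SD after infant covariates, the bias is about 0.02 to 0.09 SD. That is small beside the planned effect of 0.50, but a larger sample does not reduce it. Its direction depends on whether consenters' infants do better or worse. It also assumes that matched comparators mirror the pool; a match that favoured consented comparators would shrink it.

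Whether costs are matched or weighted is a lesser inconsistency, but the two paragraphs must agree.

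**What to change.** 1. For growth and cost, build the score only from infant variables measured by eligibility and held for every sub-cohort. Put NICU in the score or match exactly within NICU. Restate the balance goal for these two outcomes accordingly.
2. Add a consented-versus-consented analysis of both outcomes with parent characteristics in the score, as a check on consent selection. It needs no new data.
3. Where the sites' approvals permit, extend the de-identified individual EHR and cost extract to eligible non-consented infants in the Planning and Executing windows (about 542 − 379 = 163 per window at 70% enrolment), so that both sides are all eligible infants. Permission has to be confirmed first.
4. State once whether hospital costs are matched or weighted, and use the same term in the cost model. Weighting the full sample is an optional gain in precision, not a correction.

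The cost is that parent variables are not adjusted for in the main growth and cost models; item 2 partly covers this. Items 1, 2 and 4 need only text changes and data already planned. Item 3 needs a wider data request. The article reports no subjects enrolled at submission, so all four could be settled before outcomes are seen.
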